# Does a high dietary intake of resistant starch affect glycaemic control and alter the gut microbiome in women with gestational diabetes? A randomised control trial protocol

**DOI:** 10.1186/s12884-021-04366-4

**Published:** 2022-01-18

**Keywords:** Gestational diabetes, Diet therapy, Resistant starch, Gut microbiome, Fasting glucose, Short-chain fatty acids

## Abstract

**Background:**

Gestational Diabetes Mellitus (GDM) is prevalent with lasting health implications for the mother and offspring. Medical nutrition therapy is the foundation of GDM management yet achieving optimal glycaemic control often requires treatment with medications, like insulin. New dietary strategies to improve GDM management and outcomes are required.

Gut dysbiosis is a feature of GDM pregnancies, therefore, dietary manipulation of the gut microbiota may offer a new avenue for management. Resistant starch is a fermentable dietary fibre known to alter the gut microbiota and enhance production of short-chain fatty acids. Evidence suggests that short-chain fatty acids improve glycaemia via multiple mechanisms, however, this has not been evaluated in GDM.

**Methods:**

An open-label, parallel-group design study will investigate whether a high dietary resistant starch intake or resistant starch supplement improves glycaemic control and changes the gut microbiome compared with standard dietary advice in women with newly diagnosed GDM. Ninety women will be randomised to one of three groups - standard dietary treatment for GDM (Control), a high resistant starch diet or a high resistant starch diet plus a 16 g resistant starch supplement. Measurements taken at Baseline (24 to 30-weeks’ gestation), Day 10 and Day 56 (approximately 36 weeks’ gestation) will include fasting plasma glucose levels, microbial composition and short-chain fatty acid concentrations in stool, 3-day dietary intake records and bowel symptoms questionnaires. One-week post-natal data collection will include microbial composition and short-chain fatty acid concentrations of maternal and neonatal stools, microbial composition of breastmilk, birthweight, maternal and neonatal outcomes. Mixed model analysis of variance will assess change in glycaemia and permutation-based multivariate analysis of variance will assess changes in microbial composition within and between intervention groups. Distance-based linear modelling will identify correlation between change in stool microbiota, short-chain fatty acids and measures of glycaemia.

**Discussion:**

To improve outcomes for GDM dyads, evaluation of a high dietary intake of resistant starch to improve glycaemia through the gut microbiome needs to be established. This will expand the dietary interventions available to manage GDM without medication.

**Trial registration:**

Australian New Zealand Clinical Trial Registry, ACTRN12620000968976p. Registered 28 September 2020

**Supplementary Information:**

The online version contains supplementary material available at 10.1186/s12884-021-04366-4.

## Background

Gestational Diabetes (GDM) is a state of glucose intolerance first discovered in pregnancy via routine screening undertaken between 24 and 28 weeks of gestation [1]. It is largely a disease of insulin resistance (IR) with the prevalence increasing in parallel with increasing rates of obesity [2]. Optimal glycaemic control reduces many of the risks associated with GDM [3–5] including preeclampsia, macrosomia, large for gestational age, shoulder dystocia and neonatal hypoglycaemia [2, 6]. Offspring of women with GDM also have a higher risk of obesity and impaired glucose metabolism [2, 7–10]. Mothers with a history of GDM have an increased risk of developing cardiovascular disease [11] and type 2 diabetes (T2DM) [12].

Current evidence-based dietary strategies are often insufficient to optimise glycaemia [13] therefore, in some populations, more than half of GDM women require pharmacotherapy to control their blood glucose [14–17]. This increases the burden to the woman and health system through additional monitoring and clinic appointments to ameliorate the risk [18]. Hence, new dietary strategies are required to improve outcomes for women and their offspring [5] and to reduce health expenditure [18].

Similar to T2DM [19, 20], gut dysbiosis has been reported as a feature of GDM pregnancies and associated with higher blood glucose levels [21–23]. Evidence to support the relationship between diet, the gut microbiota, IR and glycaemic control in T2DM is strengthening [24–30]. Hence, specific changes to the diet can modify the gut microbiota [31, 32] suggesting that dietary modifications which impact the maternal gut microbiota and metabolome are potential therapies to improve glycaemia in GDM [21, 33–36].

Gut microbiota and glycaemic control are known to be altered by fermentable dietary fibres such as resistant starch (RS) [28, 29, 37, 38]. A systematic review by Colantonio, Werner and Brown [29] concluded that foods with prebiotic properties, such as RS, may improve glycaemic control in women with T2DM. More specifically, a meta-analysis of RS supplementation by Wang et al. [28] showed improvements in fasting glucose and IR, particularly in overweight or obese people with diabetes. Microbial fermentation of RS increases the production of short chain fatty acids (SCFA) [39]. SCFA are thought to improve glycaemic control through multiple mechanisms [20], discussed later, suggesting that the manipulation of the microbiome using RS may be a novel therapeutic option for reducing the severity of GDM.

This study will evaluate whether a high dietary RS intake from diagnosis with GDM can improve maternal glycaemic control; impacts the maternal and/or neonatal gut microbiota, faecal SCFA production, maternal and neonatal health outcomes; and collect information to determine the health economic benefits of improvement of dyads health outcomes that result from this intervention.

We hypothesise that compared with standard GDM dietary advice, women with a high dietary intake of RS from the diagnosis of GDM will show a reduction in fasting blood glucose (FBG) levels and other measures of glycaemic control. This will reduce the percentage of women who require insulin and improve maternal and foetal outcomes.

## Methods

### Overview of study design

An open-label, parallel-group design study will be used to investigate whether a higher RS intake from diagnosis of GDM changes the gut microbiome and improves glycaemic control compared with standard dietary advice. Educating women to consume a diet consistent with evidence-based recommendations for the dietary management of GDM [40] was chosen as the comparator group as it is safe for participants and this study aims to evaluate whether the interventions are more effective than usual care.

Participants will enter the trial at diagnosis with GDM between 24 and 30 weeks of gestation. Informed written consent will be obtained by the Principal Investigator (PI) prior to randomisation into one of three dietary treatment groups – standard dietary treatment for GDM (Control), a high RS diet (RS Diet) or a high RS diet plus an RS supplement (RS Supp). The dietary intervention will continue until delivery. Measurements will be taken at Baseline over Days 1–3 (where they will be between 24 to 36-weeks’ gestation), Day 10, Day 56 (approximately 36-weeks’ gestation) and 1-week after delivery (Fig. 1).

**Fig. 1 Fig1:**
[figure not shown]
Flow diagram of study design, participant recruitment and journey. *Note:* GDM = Gestational Diabetes Mellitus

### Study population

Participants will be women who are newly diagnosed with GDM and plan to deliver their baby at a tertiary hospital in Western Australia, where all study visits and routine antenatal care will be undertaken. Inclusion criteria include women diagnosed with GDM through a routine 75 g Oral Glucose Tolerance Test (OGTT) between 24 and 30 weeks of pregnancy and ≥ 18 years of age. A diagnosis of GDM is made using the International Association of Diabetes in Pregnancy Study Groups (IADPSG) diagnostic criteria of one or more values reaching the following levels – Fasting glucose ≥5.1 mmol/L, 1-h ≥ 10.0 mmol/L, 2-h ≥ 8.5 mmol/L [41].

Participants will be excluded if they have an early diagnosis of GDM before 24 weeks; Overt Diabetes in Pregnancy; Type 1 Diabetes; T2DM; poorly controlled hypothyroidism; Graves’ Disease; twin pregnancy; breastfeeding; vegetarian; vegan; irritable bowel syndrome; inflammatory bowel disease; previous bariatric surgery; history of an eating disorder; allergy to adhesives; antibiotic use in the past 3 months; use of steroids, antipsychotics, metformin, laxatives, fibre supplements or probiotic supplement; any major medical disorder; any psychosocial issues likely to impact on ability to adhere to study protocol.

Demographic information will be collected from the digital medical record (DMR) and participants will complete a demographic questionnaire at Baseline to obtain information on ethnicity, medical and obstetric history, medication and dietary supplement usage.

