### Sample size

In a study by Asemi et al. [42], the average woman with GDM has a mean FBG of 5.175 ± 0.86 mmol/L. In RS supplementation trials, a difference in FBG as large as 0.4 mmol/L has been observed between control and RS supplemented groups [38]. This study aims to demonstrate a reduction in FBG of 0.3 mmol/L, which corresponds to a small to medium Cohen’s effect size (*d* = 0.35). Based on a repeated-measures design with three groups (Control, RS Diet, RS Supp) and three time points (Baseline, Day 10 and approximately Day 56), a minimum sample size of 69 (i.e., 23 per group) is required to detect a small to medium within-between interaction effect (Cohen’s *f* = 0.175) at 80% power and 5% level of significance. Allowing for an attrition rate of around 30%, the final total sample size required is 90 (i.e., 30 per group). Women who commence insulin therapy will remain in the study.

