### Randomisation

Stratified randomisation of participants based on pre-pregnancy Body Mass Index (BMI) category will be utilised. BMI categories are Healthy (BMI 18.5–24.9 kg/m^2^), Overweight (BMI 25–29.9 kg/m^2^) and Obese (BMI ≥ 30 kg/m^2^). A computer-generated random sequence was created by a statistician and repeating blocks of three groups per three BMI categories were used to generate group allocation order. Eligible participants will be randomised by the PI to the next predetermined group, sequentially as consented. Neither the participants nor the investigators will or can be blinded to the treatment allocated.

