### Primary outcome

#### Fasting blood glucose

The primary outcome of this study will be a reduction in median FBG from Baseline, within and between groups. Baseline FBG will be recorded from the diagnostic OGTT results [41]. Subsequent venous blood samples will be collected after an overnight fast at Day 10 and Day 56 and analysed for FBG following protocols from the National Association of Testing Laboratories. FBG within treatment targets (< 5.1 mmol/L) [49] is the measure of glycaemic control that has been most difficult to achieve with standard GDM diet and lifestyle interventions and therefore the variable most likely to indicate the need for medical therapy, such as insulin [50]. If FBGL below 5.1 mmol/L is not achieved by Day 10, insulin therapy will commence. Participants treated with insulin will remain in the study.

Routinely women will receive self-monitoring of blood glucose (SMBG) education. Participants will be provided with an SMBG meter and instructed on measuring blood glucose levels four times daily (FBG and 2-h post-prandially). The SMBG meters used will be either Contour Next (Ascensia Diabetes Care, Switzerland), Accu-Chek Guide (Roche Diabetes Care, Switzerland) or One Touch Verio (LifeScan, USA) and meet International Organization for Standardization (ISO) standards for accuracy. Data from these models will be uploaded via the Diasend Uploader (Glooko, USA). FBG will be monitored on the first 2 days and averaged to provide a Baseline measure. This will be compared to the moving averages over the subsequent 8 days of testing, and then again between Days 48 and 56, across the three dietary groups (Control, RS Diet and RS Supp) using mixed model ANOVA with group-by-time interaction.

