#### Requirement for insulin treatment

Data from the participants’ DMR will determine the percentage of women requiring insulin to control blood glucose levels at Day 10 and Day 56 compared to the control group. Participants who require insulin will remain in the study and all samples will be collected. The commencement of insulin to manage glycaemia requires more health care monitoring and intervention, adding burden to the woman and the health care system [18].

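### The insulin comparison takes no stated account of OGTT fasting glucose, although women can enter on either side of the 5.1 mmol/L cut-off that triggers insulin

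*Protocol article*

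**What the plan says.** - **Eligibility (Study population).** The diagnosis rests on "diagnostic criteria of one or more values reaching the following levels": fasting ≥5.1, 1-h ≥10.0 or 2-h ≥8.5 mmol/L. Fasting glucose below 5.1 is therefore admitted.
- **Expected level (Sample size).** The plan takes from an outside study that "the average woman with GDM has a mean FBG of 5.175 ± 0.86 mmol/L".
- **Allocation (Randomisation).** "Stratified randomisation of participants based on pre-pregnancy Body Mass Index (BMI) category will be utilised". No other factor is named.
- **Cut-off (Fasting blood glucose).** The section takes baseline fasting glucose from the diagnostic OGTT, so it is known before allocation. It then states: "If FBGL below 5.1 mmol/L is not achieved by Day 10, insulin therapy will commence".
- **Insulin outcome (Requirement for insulin treatment).** The measure is the "percentage of women requiring insulin to control blood glucose levels at Day 10 and Day 56 compared to the control group". No adjustment is mentioned.
- **Covariates (Statistical analyses).** For the glucose model the section names age, pre-pregnancy BMI, parity and ethnicity, as examples. OGTT fasting glucose is not named.

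**The concern.** Fasting glucose at entry is the same quantity, on the same cut-off, that decides insulin at Day 10. It should therefore be a strong predictor of the insulin outcome, and every woman has it on record before she is allocated. With about 30 women per arm, chance can put noticeably more women above the cut-off in one arm than in another. Neither the allocation nor the stated insulin comparison takes this into account. Fewer women needing insulin is part of the trial's hypothesis, so a comparison that carries avoidable noise from a known baseline variable is weaker than it needs to be.

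**Working it through.** **The plan's own figure.** The target is 0.3 mmol/L ("This study aims to demonstrate a reduction in FBG of 0.3 mmol/L"), so d = 0.3/0.86 = 0.349 and f = 0.35/2 = 0.175. For the within-between interaction with k = 3 groups and m = 3 times, λ = f²·N·m/(1−ρ), with df (k−1)(m−1) and (N−k)(m−1). The document gives no ρ. At an assumed ρ = 0.5 and N = 69, λ = 0.030625 × 69 × 3/0.5 = 12.7 on 4 and 132 df. Power is 0.811, and 69 is the smallest multiple of three that reaches 80%. The stated figure is reproduced. The repeated measures are "three time points (Baseline, Day 10 and approximately Day 56"), so Baseline is part of the primary model. I use ρ = 0.5 as the central value below and 0.3-0.7 as the range.

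**Step 1. Share entering below 5.1.** Assume normality: Φ((5.1 − mean)/SD).

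| Mean | SD 0.5 | SD 0.86 |
|---|---|---|
| 5.175 | 44.0% | 46.5% |
| 5.4 | 27.4% | 36.4% |

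At the cited values, 0.465 × 90 ≈ 42 women, or about 14 of 30 per arm. The mean of 5.4 and the SD of 0.5 are my own sensitivity values.

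**Step 2. Chance imbalance.** Take the number at or above 5.1 in each arm as Binomial(30, 0.535), independent between arms. For one RS arm against Control, P(difference ≥5 women) = 0.244. Five women in 30 is 17 percentage points. This ignores any balance that the BMI strata bring. The documents give no correlation between BMI and fasting glucose. The SD of the difference in counts is √(60 × 0.465 × 0.535) = 3.9 women. At a 27.4% share it is √(60 × 0.274 × 0.726) = 3.5, so the probability is lower there.

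**Step 3. What a five-woman gap does to insulin need.** Assume no treatment effect, the same N(5.175, 0.86) at Baseline and Day 10, bivariate normality, and insulin decided only by fasting glucose ≥5.1 at Day 10. The shift is 5/30 times the difference between the two conditional probabilities.

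| ρ | P(≥5.1 at Day 10), entered ≥5.1 | Same, entered <5.1 | Difference | Shift in arm percentage |
|---|---|---|---|---|
| 0.3 | 62.5% | 43.1% | 19.4 | 3.2 points |
| 0.5 | 69.0% | 35.7% | 33.3 | 5.5 points |
| 0.7 | 76.4% | 27.1% | 49.3 | 8.2 points |

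For scale, the standard error of a crude difference between two arms of 30 is √(2 × 0.535 × 0.465/30) = 12.9 points.

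**Step 4. Gain from adjusting the insulin comparison.** Compare the variance within entry categories with the total variance. At ρ = 0.5, within = 0.465 × 0.357 × 0.643 + 0.535 × 0.690 × 0.310 = 0.221, and total = 0.535 × 0.465 = 0.249. Then 1 − √(0.221/0.249) ≈ 6%. Over ρ = 0.3-0.7 the standard error of the risk difference falls by about 2-13%.

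**Step 5. Would a stratum help the primary outcome?** This was simulated with two arms of 30, ρ = 0.5 and 10,000 runs. Stratifying on <5.1 versus ≥5.1 lowers the SD of a change-score estimate from 0.220 to 0.206 mmol/L, about 6%. With baseline adjustment the SD is 0.193 unstratified and 0.196 stratified, so nothing is gained.

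**The case against.** The main objections, and what stands of each:

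- **Randomisation is intact.** Chance imbalance is not bias, and ordinary standard errors allow for it. Stratifying on BMI alone is a legitimate choice that contradicts nothing in the document. This stands in full.
- **The shift is modest.** It is 3-8 points against a standard error of 12.9, in a secondary outcome. This stands, and it sets the weight of the point.
- **The analysis may be adjusted anyway.** The section on insulin gives a measure and a comparator but no test, the covariate list is open-ended, and an analysis plan may settle it. This stands too. The point is therefore a recommendation about a comparison stated only as a percentage. It does not claim that adjustment is ruled out.
- **The 46.5% is borrowed.** It assumes normality and that an outside study's mean and SD, reported without its diagnostic criteria, fit this trial. Hence the range of 27-47%.

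Three stronger readings are tempting, and the documents do not support them.

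1. A reader might infer that the driver of the primary outcome is left to chance. The primary outcome is change from Baseline, with Baseline a repeated measure in the model, and Step 5 shows that an extra stratum adds almost nothing. The Fasting blood glucose section takes Baseline from the OGTT, whereas Statistical analyses takes it from self-monitoring on the first two days. That needs reconciling separately, but either way a fasting starting value is in the model.
2. A reader might infer that the treatment effect is diluted. If RS worked only at or above 5.1, the pooled effect would be 0.3 × 0.535 = 0.16 mmol/L. Nothing in the document says that it works only there.
3. A reader might infer that a null result could not be interpreted. OGTT fasting glucose is recorded for every woman, so the effect by entry level can be examined. Women who qualify on post-load values also fit the post-prandial, microbiota and SCFA aims.

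**Conclusion.** The point holds for the insulin comparison and only there. Between about 27% and 47% of women may enter below the cut-off that later decides insulin. A gap of five or more women between an RS arm and Control has a probability of about 24% at the cited mean and SD, and would move expected insulin need by about 3-8 percentage points with no treatment effect. Adjusting for the entry value removes that component and lowers the standard error by about 2-13%. These figures rest on normality, an assumed baseline to Day 10 correlation of 0.3-0.7, insulin decided by Day 10 fasting glucose alone, and no help from the BMI strata. The issue is precision and chance imbalance, not bias or an error in the plan. It is a worthwhile improvement that needs no new data, and it does not threaten the primary analysis.

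**What to change.** 1. State that insulin need will be compared between each RS arm and Control adjusted for, or stratified by, OGTT fasting glucose together with BMI category. The continuous value is preferable, with <5.1 versus ≥5.1 mmol/L as the simpler form. Report a risk difference (stratified, or standardised from a regression model) with its confidence interval, because the gain in Step 4 applies on that scale. Report the crude percentages beside it.
2. Optionally, add one supportive group-by-OGTT-fasting-glucose contrast for fasting glucose, labelled in advance as imprecise.
3. Optionally, if the allocation list can still be changed, add the fasting category as a second stratum. This gives 3 × 2 = 6 strata of about 15 women on average, with some incomplete blocks. It is not needed if item 1 is adopted.

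The cost of item 1 is a sentence in the analysis section, using a value that the trial already records. Eligibility, sample size and clinical management stay as they are.

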### Sample size

In a study by Asemi et al. [42], the average woman with GDM has a mean FBG of 5.175 ± 0.86 mmol/L. In RS supplementation trials, a difference in FBG as large as 0.4 mmol/L has been observed between control and RS supplemented groups [38]. This study aims to demonstrate a reduction in FBG of 0.3 mmol/L, which corresponds to a small to medium Cohen’s effect size (*d* = 0.35). Based on a repeated-measures design with three groups (Control, RS Diet, RS Supp) and three time points (Baseline, Day 10 and approximately Day 56), a minimum sample size of 69 (i.e., 23 per group) is required to detect a small to medium within-between interaction effect (Cohen’s *f* = 0.175) at 80% power and 5% level of significance. Allowing for an attrition rate of around 30%, the final total sample size required is 90 (i.e., 30 per group). Women who commence insulin therapy will remain in the study.

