A limitation of this study is that food will not be provided to the participants which may limit compliance with a high RS diet. However, a positive result would indicate that this dietary intervention is a practical and achievable intervention to incorporate into GDM management strategies. Periodic assessment of glucose is also a limitation of the study as it only estimates overall glycaemic control but is the most frequently used method in the management of GDM, whereas continuous blood glucose monitoring would assess the overall exposure of the foetus to glucose. Funding for continuous blood glucose sensors is not yet available, therefore, an opportunity to identify any overall glycaemic benefit through time-in-range values may be missed. The study is adequately powered to detect improvements in FBG and microbial changes (based on changes in faecal SCFA) but not for other outcomes such as rates of LGA, macrosomia, neonatal hypoglycaemia and NICU admissions.

This will be the first study to evaluate RS intervention in GDM management. If a high dietary intake of RS is shown to favourably alter the GDM microbiome and results in improved glycaemic control, this will expand the dietary interventions available to manage GDM without pharmacotherapy, reducing the burden on the mother and the healthcare system. If a more favourable maternal gut microbiota is found to persist post-partum and is transferred to the neonate, longer-term health outcomes for mother and child may be enhanced.

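### The 80% power belongs to an interaction effect worth about 0.68 mmol/L, not to the stated target of 0.3 mmol/L, for which power is about 20% under the assumptions that reproduce N = 69

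*Protocol article*

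**What the plan says.** The Sample size section of the protocol article takes from an earlier study a "mean FBG of 5.175 ± 0.86 mmol/L" and states the aim: "This study aims to demonstrate a reduction in FBG of 0.3 mmol/L", "which corresponds to a small to medium Cohen’s effect size (*d* = 0.35"). The calculation is for a repeated-measures design with "three groups (Control, RS Diet, RS Supp) and three time points (Baseline, Day 10 and approximately Day 56"). Its result is that "a minimum sample size of 69 (i.e., 23 per group) is required to detect a small to medium within-between interaction effect", with "Cohen’s *f* = 0.175) at 80% power and 5% level of significance". The same section cites 0.4 mmol/L as the upper end of the differences seen in supplementation trials.

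The Primary outcome and Statistical analyses sections both name the group-by-time interaction as the analysis. Statistical analyses repeats 0.3 mmol/L as the reduction to be assessed. The limitations paragraph of the Discussion concludes: "The study is adequately powered to detect improvements in FBG and microbial changes (based on changes in faecal SCFA").

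**The concern.** The target and the effect size used for the sample size stand in consecutive sentences, as if they were one quantity in two notations. The figures suggest how they were linked: 0.35/2 = 0.175. Halving d gives Cohen's f when two equal groups are compared on a single mean. The f of a within-between interaction is a different quantity. It is the root mean square of what remains in the 3 × 3 table of means after row and column averages are removed, divided by the SD. A fall in one or two arms after baseline leaves much smaller residuals than d/2 implies.

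If so, the 80% does not apply to 0.3 mmol/L. The diet could lower fasting glucose by exactly the target and the interaction test would still probably be non-significant. A reader who relies on the Discussion would then take that result as evidence of no effect from an adequately powered trial.

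**Working it through.** **Inputs from the Sample size section.** Target 0.3 mmol/L, SD 0.86, d = 0.35, f = 0.175, 3 groups, 3 times, α = 0.05, power 0.80, N = 69.

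**Assumptions.** The within-person correlation ρ is not stated. Equal correlation between all visits (sphericity) is assumed.

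**Test.** Noncentral F for the interaction, with k = 3 groups and m = 3 times:
- λ = f² × N × m / (1 − ρ)
- df1 = (k − 1)(m − 1) = 4
- df2 = (N − k)(m − 1)

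**Step 1: reproduce the plan's figure.** With f = 0.175 and ρ = 0.5:
- N = 69: λ = 0.030625 × 69 × 3 / 0.5 = 12.68, df2 = 132, power 0.811.
- N = 66: power 0.790.

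So 69 is the smallest total with equal groups that reaches 80%. Other correlations do not return it: ρ = 0.4 gives 81 and ρ = 0.6 gives 57. The step from f = 0.175 to 69 is therefore correct at ρ = 0.5.

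**Step 2: the interaction f for 0.3 mmol/L.** Let control stay at 0, 0, 0 and both resistant-starch arms follow 0, −0.3, −0.3. After removing row and column means, the residuals are:

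| | Baseline | Day 10 | Day 56 |
|---|---|---|---|
| Control | −0.133 | 0.067 | 0.067 |
| RS Diet | 0.067 | −0.033 | −0.033 |
| RS Supp | 0.067 | −0.033 | −0.033 |

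Their root mean square is (2/9) × 0.3 = 0.0667 mmol/L, so f = 0.0667 / 0.86 = 0.0775. An effect in RS Supp only gives the same value.

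**Step 3: power for 0.3 mmol/L at N = 69, SD 0.86.** At ρ = 0.5, λ = 0.0775² × 69 × 3 / 0.5 = 2.49.

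| ρ | 0.3 | 0.5 | 0.7 | 0.8 | 0.9 |
|---|---|---|---|---|---|
| Power | 15% | 20% | 32% | 47% | 80% |

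A simulation of the interaction test at ρ = 0.5 gave 20.6%. With all 90 women analysed, power at ρ = 0.5 is 25.6%.

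**Step 4: the difference that f = 0.175 represents.** 0.175 × 0.86 / (2/9) = 0.677 mmol/L, sustained at both visits. Simulated power at that difference is 81%.

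**Step 5: other patterns at ρ = 0.5, N = 69.**
- Full effect at Day 56 only, in both arms: 20%.
- Half the effect at Day 10 and all of it at Day 56, in both arms: 16%.
- Half the effect in RS Diet and all of it in RS Supp, at both visits: 16%.
- Both halvings together: 13%.

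**Step 6: a smaller SD.** Purely for illustration, take SD 0.6 and ρ = 0.7. Then f = 0.0667 / 0.6 = 0.111, λ = 0.111² × 69 × 3 / 0.3 = 8.52, and power is about 62%.

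**The case against.** The strongest reply is that 20% is not a property of the trial. The article gives neither a correlation nor a table of expected means, and it never says that f was obtained by halving d. The value ρ = 0.5 shows what was probably entered in the calculation, not how fasting glucose will behave in these women. All of this stands, so the power must be given as a range. It does not rescue the claim. Reaching 80% for 0.3 mmol/L with SD 0.86 needs ρ near 0.9, and at that correlation f = 0.175 would not require anything like 69. No single correlation supports both the stated N and the stated target.

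A second reply is that the venous samples are single readings, whereas the mixed model described in Primary outcome and Statistical analyses uses self-monitored values over several days. Averages carry less within-person noise, so the SD may be smaller and ρ higher. This also stands, and Step 6 shows that it could matter. But the article sizes the trial on SD 0.86 and gives no SD for averaged readings.

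Two stronger readings are tempting. One is that the Discussion's power claim for microbial change and faecal short-chain fatty acids is equally wrong. The documents do not show that. A condensed article may leave that calculation to a fuller protocol, and nothing printed contradicts it. The other is that leaving out the correlation is itself an error. That too is a common omission in an article. It matters here only because a value is needed to check the figures.

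**Conclusion.** The concern holds as an effect-size conversion error. The 69 follows from f = 0.175, but f = 0.175 does not follow from 0.3 mmol/L in a 3 × 3 interaction. It represents about 0.68 mmol/L, more than twice the target and above the 0.4 mmol/L the protocol cites.

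For the target itself, power at 69 completers is about 20% if SD is 0.86, ρ is 0.5 and the fall is present at both visits in one or both resistant-starch arms. It is 15% to 47% over ρ from 0.3 to 0.8, and lower if the effect is gradual or partial. Less noisy averaged readings could raise it, to about 62% in the illustration.

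A reader might infer that power is 20% whatever the data look like. The documents do not support so flat a figure. They do show that the stated 80% cannot be attached to 0.3 mmol/L on the protocol's own inputs. The Discussion's statement of adequate power for fasting glucose therefore lacks support for the target the trial sets itself.

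**What to change.** 1. **Sample size section.** State that 69 completers give 80% power for an interaction of f = 0.175, which corresponds to about 0.68 mmol/L sustained at Day 10 and Day 56 with SD 0.86, and name the assumed correlation of 0.5. Then give power for 0.3 mmol/L as a range over stated correlations and SDs: about 20% at ρ = 0.5 and SD 0.86, with the values at other settings beside it.
2. **Discussion, limitations.** Remove the description of the trial as adequately powered as far as it concerns fasting glucose.
3. **Reporting.** Present the fasting glucose effect with confidence intervals, so that a non-significant interaction is not read as evidence of no effect.

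This needs no extra patients and no change to visits or treatment. The cost is that the stated power becomes less favourable.

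### Ninety women allow for about 23% attrition, not the stated 30%: a 30% loss leaves 63, six below the plan's own minimum of 69

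*Protocol article*

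**What the plan says.** All the figures are in the Sample size section of the protocol article. For a design with three groups and three time points, it states that "a minimum sample size of 69 (i.e., 23 per group) is required". The planned test is of the group-by-time interaction, with Cohen's f set to 0.175, alpha to 5% and power to 80%. The allowance for loss comes next: "Allowing for an attrition rate of around 30%, the final total sample size required is 90 (i.e., 30 per group"). The Methods part of the abstract repeats the total: "Ninety women will be randomised to one of three groups". The article gives no other attrition figure, no inflation formula, and no correlation between repeated measurements. The same section keeps women who start insulin in the study, so they are not part of the 30%.

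**The concern.** The purpose of an attrition allowance is that the minimum number remains after the expected loss. Here the minimum, the expected loss and the total are all stated, so they can be checked against each other, and the total is too small for the other two. The calculation concerns fasting glucose, the primary outcome, and the Discussion relies on it when it describes the study as adequately powered for that outcome. A reader who takes the section at face value will believe that 30% of women can be lost with the stated minimum intact. That margin is used up at about 23%.

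**Working it through.** **Inputs (all from Sample size).** Minimum 69, or 23 per group; attrition around 30%; total 90, or 30 per group; f = 0.175; alpha 5%; power 80%; 3 groups; 3 time points.

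**1. Reproducing the minimum of 69.** For the group-by-time interaction F test, the noncentrality is λ = f² × N × m / (1 − ρ), with m = 3, df1 = (3 − 1)(3 − 1) = 4 and df2 = (N − 3) × 2. The article does not state ρ. Assuming ρ = 0.5 and sphericity:
- N = 68 is the smallest total reaching 80%, and 69 is the smallest with equal groups.
- At N = 69, λ = 0.030625 × 69 × 3 / 0.5 = 12.68 and power is 81.1%.

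So 69 is reproduced under these assumptions.

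**2. Reproducing the total of 90.**
- Adding 30%: 69 × 1.3 = 89.7, rounded up to 90; per group 23 × 1.3 = 29.9, rounded up to 30. Both stated figures are reproduced.
- Dividing by the fraction retained: 69 / 0.7 = 98.6, rounded up to 99; per group 23 / 0.7 = 32.9, rounded up to 33. Neither stated figure is reproduced.

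**3. What 90 leaves.**
- 90 × 0.7 = 63 in total; 30 × 0.7 = 21 per group.
- Shortfall: 69 − 63 = 6 in total, 2 per group.
- Largest loss that still leaves 69: 1 − 69/90 = 23.3%.

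| Attrition | Left from 90 | Needed to keep 69 |
|---|---|---|
| 20% | 72.0 | 86.25 |
| 23.3% | 69.0 | 90.0 |
| 25% | 67.5 | 92.0 |
| 28% | 64.8 | 95.8 |
| 30% | 63.0 | 98.6 |

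Steps 2 and 3 need no assumption about the correlation.

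**4. Power with 63 women, completers only.** At ρ = 0.5, λ = 0.030625 × 63 × 3 / 0.5 = 11.58 and power is 76.8%, against 81.1% at 69. The absolute level depends strongly on the unstated correlation:

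| Assumed ρ | Power at 69 | Power at 63 |
|---|---|---|
| 0.3 | 65% | 60% |
| 0.4 | 73% | 68% |
| 0.5 | 81% | 77% |
| 0.6 | 90% | 86% |
| 0.7 | 97% | 95% |

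**5. Power if partial records are used.** This takes 90 randomised and 63 reaching Day 56, with a baseline value for every woman. It assumes ρ = 0.5, compound symmetry, data missing at random, and an effect scaled to f = 0.175.
- Effect present by Day 10 and sustained: about 89% if all losses follow Day 10, and about 86% if half precede it.
- Effect growing evenly over the three visits: about 82%.
- Effect appearing only at Day 56: about 78%.

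**The case against.** The strongest reply is that women who leave are not lost to the analysis.
- The Statistical analyses section plans a linear mixed model with a group-by-time interaction, which can use incomplete records.
- Data management allows data from women who later withdraw to be used unless they withdraw consent for it.
- The Primary outcome section takes baseline fasting glucose from the diagnostic test, so every randomised woman has a value.
- Recruitment lets women who stop giving stool and urine samples still give fasting glucose.

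This stands as far as power is concerned. Step 5 shows that, under its assumptions, 90 women with 63 reaching Day 56 could have power from about 78% to 89%. A reader might infer that the trial will have only 77% power, or that it is underpowered. The documents do not support either inference. The 77% is a completers-only value at a correlation of 0.5, which the article does not state and which is inferred only because it reproduces 69.

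The reply does not rescue the sentence itself. The article sets a minimum of 69 and inflates it for attrition; it does not cite partial data as the reason for 90. Nor does the word "around" close the gap, because 23% is not a natural reading of around 30%, and at 25% the number left is already 67.5.

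A reader might also take it as established that the allowance was calculated as 69 × 1.3. That is a likely explanation, since it gives both 90 and 30 per group, but the article does not show the step. The shortfall is the same however 90 was reached.

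Finally, the shortfall is small: two women per group and about four percentage points of completers-only power at ρ = 0.5.

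**Conclusion.** The point holds as an error in a stated figure. Ninety randomised women allow for about 23% attrition. At the stated 30%, 63 (21 per group) would complete, 6 below the minimum that the plan sets for 80% power, and keeping 69 would need 99 (33 per group). This rests only on the article's own three numbers.

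The size of any power loss is not established. It depends on an unstated correlation, on when women leave, and on how far the mixed model uses their partial data. Severity is moderate: the statement should be corrected, but the design and the analysis are not called into question.

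**What to change.** Keep 90 and correct the sentence in Sample size, for example: *Ninety women (30 per group) will be randomised, which allows for about 23% attrition from the minimum of 69. At 30% attrition about 63 women (21 per group) would complete, which is below the minimum of 69 for 80% power.* If the 30% allowance is to be held instead, the number to state is 99 (33 per group), in this section and in the abstract.

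If a power figure is added, label it as completers-only under an assumed correlation: about 77% at 0.5, with a range of 60% to 95% for 0.3 to 0.7. Note beside it that the planned mixed model may recover part of the loss. The Discussion's statement on adequate power for fasting glucose should carry the same condition.

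Keeping 90 costs one or two sentences and a less favourable stated margin, with no change to conduct. Moving to 99 means recruiting nine more women.
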